#### Qualitative explorations

We will determine the sample size for the qualitative segment of the study through data saturation. As a general guide, we propose conducting 8–10 interviews per round with frontline health workers, 10–15 with family members, 3–4 with district-level managers and supervisors, and 3–6 with central-level managers and policymakers.

#### Other data collection methods

We will extract data from service registers twice a week in all CCs throughout the study implementation period. We will also assess all CCs from the study sites and interview all CHCPs for knowledge assessment at baseline and endline.

### Quality control and assurance

We will ensure data quality through regular monitoring and data checks. Two observers will independently validate 2% of all records, with continuous feedback throughout the data collection process to the data collectors. For quality assurance, staff from the icddr,b office, along with designated field managers and personnel, will closely monitor the data collection process, while the WHO team will conduct on-site visits to oversee and support field-level implementation.

### Data security and ownership

We will assign individual identifiers to link study records or use an algorithm based on names and birth dates, where identifying information will be removed post-matching. These anonymised data will be uploaded weekly to a central web-based platform coordinated by icddr,b, and will be stored on a secure server with automatic nightly backups to an off-site location. The data will be encrypted, accessible only to the research team members. The data generated will be jointly owned by icddr,b and the WHO, and any use will require consent from both parties. In accordance with icddr,b’s data access and archival policies, they will become available for future research three years after the study completion, as recorded by the institutional review board of icddr,b, unless WHO or icddr,b specifies a shorter release period.

### Data analysis

We will use descriptive statistics to report the readiness of CCs for pneumonia case management, knowledge of CHCPs, utilisation of CCs by under-five children, and treatment compliance by caregivers, treatment failure rates, knowledge of caregivers regarding general danger signs and pneumonia danger signs, and care-seeking by caregivers for under-five children. Changes in these indicators will be presented quarterly. We will score health facility readiness based on the availability of essential items for managing pneumonia cases according to national guidelines and consultations with the clinical experts and national health managers. We will categorise facility readiness based on item availability as poor (0–50%), moderate (50–75%), and good (75–100%).

We will calculate treatment compliance based on caregiver recall of giving prescribed antibiotics from CCs at home, collected through the follow-up interviews with caregivers. Data will be analysed using Stata, version 16.0 (StataCorp LLC, College Station, Texas, USA).

We will base our qualitative analysis on a thematic approach. First, multiple researchers will code a minimal set of transcripts to establish intercoder reliability, after which a master code-list will be created for the remaining transcripts. We will compare the new and earlier data iteratively data to identify similarities and differences.

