### Study settings, period, and population

We will select two *upazilas* (sub-districts) in total: one each from the Kushtia and Dinajpur districts. From them, we will choose 20 CCs based on service availability and caseload, in consultation with national and district-level health managers. Dinajpur district covers an area of 3437.98 km^2^ and is home to 299 0128 inhabitants, resulting in a population density of 868 people per km^2^ [35]. The district has one medical college hospital, one district hospital, 12 *upazila* health complexes (sub-district hospitals), 119 union sub-centres and union health & family welfare centres (union level health centres), and 337 CCs (health outpost centres) [36]. Kushtia district has a population of 1 986 838 and covers an area of 1621.15 km^2^, leaving a density of 1073 people per km^2^ [37]. The district's health facilities include one district hospital (secondary level referral hospital), five *upazila* health complexes (sub-district hospitals), 73 union health and family welfare centres (union level health centres), and 205 CCs [36]. The study will be conducted across 24 months, where 18 months will be reserved for the delivery of the implementation package.

The study population will be under-five children presenting with pneumonia in CCs, CHCPs working in CCs, caregivers and family members of children visiting CCs, district and sub-district level health managers and supervisors and central-level health managers and policymakers.

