**Figure 3 F3:**
[figure not shown]
Theory of Change underpinning EMPIC intervention. CC - community clinic, CHCP – community healthcare provider, EMPIC - Enhanced Management of Pneumonia in Community, IMCI – Integrated Management of Childhood Illness, MoHFW – Ministry of Health and Family Welfare, PDCA – Plan-Do-Check-Act.

#### Activity 3

Health facility assessments will be conducted at baseline and end-line to evaluate the service availability and readiness of CCs, using structured tools to assess equipment, drugs, and logistics for pneumonia management, as well as CHCPs’ knowledge regarding management of childhood pneumonia. We will extract data from routine registers to evaluate recording and reporting practices, and will monitor monthly utilisation reports through central management information systems. Community follow-up of the pneumonia-classified children on the 7th and 14th days of CC visit will involve household visits by study-nurses to assess treatment failure rates and adherence to guidelines. Baseline and endline household surveys will measure caregivers' knowledge, care-seeking practices, and treatment outcomes, defining treatment failure based on specific clinical criteria.

We will explore the experiences of health managers, CHCPs, and caregivers through in-depth and key informant interviews which will focus on contextual factors, including social determinants of health, cultural beliefs, caregiver practices, and CHCPs and health system constraints (such as workload assessment) that influence care-seeking and treatment adherence. Insights from these interviews will inform iterative refinement of the intervention and interpretation of fidelity, acceptability, and adoption outcomes. This comprehensive data collection (**Table 1**) will inform continuous improvements in pneumonia management at CCs.

**Table 1 T1:** Data collection procedure throughout the study period

	Baseline	Q1	Q2	Q3	Q4	Q5	Q6	Endline
Health facility assessment	X	O	O	O	X	O	O	X
Knowledge assessment of service providers	X	O	O	O	O	O	O	X
Household survey	X	O	O	O	O	O	O	X
Data extraction	O	X	X	X	X	X	X	O
Community follow-up	O	X	X	X	X	X	X	O
Qualitative exploration	X	X	X	X	X	X	X	X

X – active data collection period for the specified activity, O – no data collection (activity not conducted during that time period

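### Quarterly change is promised for seven indicators, but four are not measured quarterly, and clinic utilisation has no stated pre-implementation period against which to allow for season

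*Protocol article*

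**What the plan says.** The Data analysis section of the protocol article opens its list of indicators with: "We will use descriptive statistics to report the readiness of CCs for pneumonia case management, knowledge of CHCPs, utilisation of CCs by under-five children". It goes on to treatment compliance, treatment failure, caregiver knowledge of danger signs, and care-seeking, which makes seven. It then says: "Changes in these indicators will be presented quarterly".

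Table 1 (Activity 3), headed "Data collection procedure throughout the study period", has eight columns: baseline, Q1 to Q6, and endline. X marks data collection and O marks none.

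- Register extraction: "Data extraction O X X X X X X O". The section on other data collection methods agrees: "We will extract data from service registers twice a week in all CCs throughout the study implementation period".
- Community follow-up, the source for treatment failure and compliance: "Community follow-up O X X X X X X O".
- The household survey and the knowledge assessment of community healthcare providers (CHCPs) are marked at baseline and endline only.
- The health facility assessment is marked at baseline, Q4 and endline. The Activity 3 text places it at baseline and endline only, and the section on other data collection methods does not mention a Q4 round either.

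A second source for utilisation is named in Activity 3: the team "will monitor monthly utilisation reports through central management information systems". This source has no row in Table 1, and no look-back period is given. On timing, the study lasts 24 months, "where 18 months will be reserved for the delivery of the implementation package". No calendar months are given for either survey.

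**The concern.** The reporting sentence covers all seven indicators, but the collection schedule does not supply quarterly values for all of them. Whoever writes the results would have to leave the statement unfulfilled for some indicators or fill the quarters from an unplanned source.

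The second issue is what a quarterly change in utilisation would mean. Utilisation of community clinics (CCs) for pneumonia-related symptoms is a secondary outcome, and the package is intended to raise care-seeking at CCs. A count of visits for pneumonia symptoms should follow pneumonia incidence. If incidence varies over the year, a rise or fall between quarters may be partly or wholly seasonal. The scheduled extraction starts under the package, so it cannot by itself show what the same months looked like before. The same question arises for pneumonia prevalence, also a secondary outcome, if it is compared between two surveys held at different times of year.

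**Working it through.** **Step 1. Measurements per indicator.** The indicators are those listed under Data analysis. Each is matched to its source in Activity 3 and its X marks in Table 1 are counted.

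| Indicator | Source | Baseline | Quarters measured (of 6) | Endline |
|---|---|---|---|---|
| CC readiness | Facility assessment | yes | 1 (Q4) | yes |
| CHCP knowledge | Knowledge assessment | yes | 0 | yes |
| Caregiver knowledge | Household survey | yes | 0 | yes |
| Care-seeking | Household survey | yes | 0 | yes |
| CC utilisation | Register extraction | no | 6 | no |
| Treatment compliance | Community follow-up | no | 6 | no |
| Treatment failure | Community follow-up | no | 6 | no |

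The first four rows cannot give a quarterly series. The last three can, but none has a scheduled value before Q1. For compliance and failure this follows from what they measure, namely the outcome of children treated under the package. For utilisation it does not, because clinic visits also took place before the package.

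**Step 2. Length of the quarterly series.** 6 quarters × 3 months = 18 months, which agrees with the stated delivery period.

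**Step 3. Same-season pairs within delivery.** In months from the start of Q1, the quarter midpoints are 1.5, 4.5, 7.5, 10.5, 13.5 and 16.5.

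- Q1 to Q5: 13.5 − 1.5 = 12 months, same season.
- Q2 to Q6: 16.5 − 4.5 = 12 months, same season.
- Q1 to Q6: 16.5 − 1.5 = 15 months, a calendar offset of 15 − 12 = 3 months.
- Q3 and Q4 have no partner 12 months away within the series.

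Comparing the first quarter with the last therefore compares different seasons. The two matched pairs lie wholly within implementation, so neither is a before-and-after comparison.

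**Step 4. Calendar offset between the surveys.** For a gap of g months, offset = min(g mod 12, 12 − g mod 12). If the surveys sit immediately before and after delivery, g is 18. In a 24-month study g can approach 24.

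| Gap g (months) | 18 | 19 | 20 | 21 | 22 | 23 | 24 |
|---|---|---|---|---|---|---|---|
| Offset (months) | 6 | 5 | 4 | 3 | 2 | 1 | 0 |

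The offset therefore lies between six months and about zero, and the article does not say where.

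**Step 5. What 12 earlier months would supply.** A run of monthly reports from month −12 to month 0 contains four quarters. Q1 and Q5 match months −12 to −9, Q2 and Q6 match −9 to −6, Q3 matches −6 to −3, and Q4 matches −3 to 0. Every implementation quarter then has a pre-implementation partner in the same calendar months.

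**The case against.** The strongest reply is that the mismatch over quarterly presentation is a wording slip, cured by one sentence, and that the rest asks a descriptive feasibility study to be something else. The article declares an implementation research design with descriptive analysis and no comparison area, and it names feasibility, fidelity, acceptability and integration as its focus. A condensed article may also leave survey dates and the look-back period to a fuller document. Much of this stands, and it rules out several stronger readings.

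- **That utilisation has no before at all.** A reader might infer this from the baseline O in Table 1. That row covers study extraction from registers. The monthly management information system (MIS) reports are a separate source with no row in the table. Use of earlier months is unstated, not excluded.
- **That the two surveys fall in opposite seasons.** That is one end of the range in step 4. No survey dates are given.
- **That a pure season effect would shift prevalence by some large factor, say 1.5- to 3-fold.** That would need a peak-to-trough ratio from outside the documents, a gap of exactly 18 months, and one survey at the peak with the other at the trough. Surveys six months apart at the two midpoints of a smooth cycle would show no seasonal difference. No expected size can be given.
- **That the care-seeking contrast is equally exposed.** The planned change from 40% to 80% is a proportion among children with suspected pneumonia in the preceding four weeks. Season changes how many such children there are more directly than it changes the share taken for care.
- **That the other CCs of the same upazilas must serve as concurrent controls.** The study CCs are chosen for service availability and caseload, so the others differ by design, and they would share upazila management. This is a debatable option, not a requirement.

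The reply does not remove the contradiction between Data analysis and Table 1, since both statements are in the article. Nor does the feasibility label remove the need for an interpretable change in utilisation, because the article itself says changes in this indicator will be presented.

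**Conclusion.** The point holds in limited form. Four of the seven indicators cannot be presented quarterly under Table 1: three have no quarterly measurement and one has a single one. This count is exact and rests on no assumption. The Q4 facility assessment appears in Table 1 but not in the text, and the two should be reconciled.

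Utilisation can be shown quarterly, but only from Q1 in the scheduled extraction, with no pre-implementation period stated for the MIS reports. Its change between quarters is open to confounding by season, with two same-season pairs among the six quarters. This rests on the assumption that childhood pneumonia is seasonal in the study area, for which the article gives no figure, so the size of any distortion is not estimated.

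The survey offset, six months to about zero, is a risk to be managed by scheduling and not a demonstrated flaw. It bears mainly on pneumonia prevalence, assuming prevalence is taken from the surveys. No claim is made about the primary outcome. The correction should be made because it is cheap and it changes what can be concluded about utilisation.

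**What to change.** 1. In Data analysis, limit quarterly presentation to utilisation, compliance and treatment failure. Report caregiver knowledge, care-seeking and CHCP knowledge at baseline and endline, and readiness at the Table 1 time points, once Table 1 and the text agree on whether there is a Q4 facility assessment.
2. Obtain the existing monthly MIS utilisation reports for the study CCs for at least 12 months before Q1. Compare utilisation during implementation with the same calendar months or quarters before it.
3. Place the baseline and endline surveys in calendar months as close to each other as the 24-month study allows, state the months, and list any remaining offset as a limitation when prevalence is compared.

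The cost is one corrected sentence and one reconciled table row, a data request to a system already being monitored, a little analysis time, and a constraint on survey dates. No new field staff are needed.

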### Dissemination plan

Upon completion, we will publish the study results in a peer-reviewed journal and present them at relevant national and international conferences and workshops. This will facilitate knowledge sharing and discussions with healthcare professionals, policymakers, and researchers, as well as provide evidence-based insights for pneumonia management in CCs. We will also develop a report on the study's methodology, findings, and recommendations for sharing with stakeholders such as government agencies, healthcare providers, and non-governmental organisations involved in child health.

## DISCUSSION

This implementation research aims to assess the feasibility of introducing EMPIC within CCs through the existing governmental health systems in Bangladesh. The goal is to improve population-based coverage of pneumonia treatment among children under the age of five and facilitate scale-up. Pneumonia-related deaths predominantly occur at the community level, where the WHO and UNICEF have established the iCCM approach for community health workers. According to the previous iCCM protocol, children aged 2–59 months presenting with fast breathing alone should receive oral amoxicillin, while those exhibiting chest indrawing or other danger signs should be referred to higher-level health facilities. Similarly, young infants aged 0–59 days with fast breathing alone or any danger sign should be directed to referral facilities by community health workers [40]. Subsequently, the WHO conducted a cluster-randomised, community-based trial across four countries in Asia and Africa, including Bangladesh, to evaluate whether community health workers could manage young infants aged 7–59 days with fast breathing alone, or children aged 2–59 months with chest indrawing pneumonia, using oral amoxicillin at home without referrals (enhanced iCCM strategy). The trial demonstrated that treating non-hypoxaemic, non-severe pneumonia with oral amoxicillin administered by community health workers was non-inferior to the standard iCCM referral-based approach [29,30]. Bangladesh is currently implementing the globally endorsed IMCI strategy, developed by the WHO and UNICEF, to manage common childhood illnesses, including pneumonia, in outpatient settings [39]. This study aims to integrate the enhanced iCCM approach into the existing IMCI framework operational in Bangladesh.

The early implementation of this strategy within a real-world programmatic context is crucial for enabling parents, community health workers, and policymakers to recognise the advantages of the enhanced iCCM approach in managing childhood pneumonia. This initiative aims to improve access to pneumonia treatment closer to home, with the anticipated benefits being: minimising the need for referrals or hospital admissions; reducing costs associated with treatment and its administration; lowering family expenses related to transportation, food, and wage loss; saving time for both families and health workers; and alleviating the burden on already overwhelmed hospital facilities.

One of the key interventions in this study is the detection of hypoxaemia by community health workers using pulse oximetry. Bangladesh is among the first LMICs to incorporate pulse oximetry into outpatient pneumonia management, following global recommendations [41,42]. However, this approach has not yet been implemented at community-level health facilities, such as CCs. Here, we will introduce pulse oximetry devices in CCs within the study areas and train community health workers on their appropriate use.

Bangladesh is among the few LMICs where community health workers have the provision to administer certain antibiotics, including oral amoxicillin. Nevertheless, consistent with global concerns, there are apprehensions in Bangladesh regarding the empirical use of antibiotics for pneumonia treatment, which may contribute to antibiotic resistance and inappropriate use in cases of viral infections [43,44]. Evidence indicates that the WHO's standard case management guidelines for pneumonia support the rational use of antibiotics in infants and children [45,46]. To mitigate the risk of improper use of oral amoxicillin by community health workers, their activities will be supervised and closely monitored by clinical supervisors.

Delayed or inadequate care-seeking remains a critical factor contributing to treatment failure and pneumonia-related mortality, particularly in resource-limited settings [47,48]. In Bangladesh, care-seeking behaviour from appropriate healthcare providers and facilities has consistently been suboptimal over the years [6]. Consequently, a key focus of the implementation package used in our study will be to improve and sustain care-seeking practices for pneumonia-related symptoms at the community level.

### Foreseeable strengths and limitations

A key strength of this study will be its implementation under the guidance of the Ministry of Health in Bangladesh. Policymakers at the national level, along with health managers from district and sub-district levels, community health workers, and their clinical supervisors, will actively participate in the planning and execution phases. Evidence from prior implementation research in Bangladesh has shown that sustained involvement of these stakeholders fosters a sense of ownership and facilitates skill development, which has proven instrumental in successfully integrating interventions into national policies and strategies [41,42,49].

This study might also have several limitations. First, the clinical diagnosis of pneumonia will not be confirmed through radiological or microbiological assessments due to the impracticality of conducting these evaluations in community settings. Second, fast breathing in young infants could be attributed to various conditions such as viral respiratory infections, high fever, bronchiolitis, or malaria, which are unlikely to respond to amoxicillin. At present, differentiating between viral, bacterial, or mixed causes of pneumonia at the time of initial assessment remains a challenge, particularly in community-based settings. Third, EMPIC’s participatory design, involving policymakers and health workers, may introduce selection bias or conflicts of interest. These risks will be mitigated through independent data collection, triangulation across multiple sources, standardised tools, and PDCA cycles, and the engagement of stakeholders, which will be essential for ownership and sustainability. Furthermore, the 18-month study period will limit the assessment of long-term changes in health-seeking behaviours, treatment coverage, and outcomes. However, this implementation research focuses on feasibility, fidelity, acceptability, and integration of EMPIC into routine health services, providing foundational insights for longer-term evaluation and scale-up. Moreover, while we aim to provide insights for adaptation in other low-resource settings by documenting key factors, such as workforce capacity, supply chains, and community acceptability, our findings will be context-specific to the selected *upazilas* in Bangladesh. Another limitation will be caregiver recall of antibiotic administration, which is subject to recall and social desirability bias. Caregivers will be asked to show the prescription and medicine bottles during follow-up visits on days 7 and 14 to confirm whether antibiotics were indeed prescribed to the children; however, this procedure will not be employed for assessing treatment compliance. As the follow-up visits will be conducted on days 7 and 14, we anticipate that it will minimise the recall bias, as the recall period is short. Finally, the evaluation framework will rely on routine register data, caregiver recall, and household surveys, which are vulnerable to reporting bias, recall bias, and data quality issues. To minimise these issues, we will triangulate information from multiple sources. Specifically, the CHCP registers will record detailed clinical and treatment data for all under-five children presenting to CCs. Study nurses will conduct structured household community follow-ups on days 7 and 14 to assess treatment adherence, antibiotic use, and clinical outcomes of the pneumonia children, cross-checking caregiver reports with register entries. Baseline and endline household surveys will capture caregiver knowledge, care-seeking practices, and treatment outcomes, while health facility assessments will monitor service readiness, equipment, and drug availability. Qualitative interviews with caregivers, CHCPs, and health managers will document implementation processes, challenges, and contextual factors. Standardised tools, rigorous data collector training, periodic audits, and PDCA cycles with twice-weekly site visits will promptly identify and resolve operational or data-quality issues. Together, these complementary monitoring and data collection strategies will provide high-quality data to guide EMPIC implementation and policy decisions, forming a structured process evaluation framework aligned with WHO implementation research outcomes, including fidelity, adoption, acceptability, appropriateness and coverage.

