### Study outcome

The primary outcome of interest is high (≥80%) and effective (patients receiving the full course of pneumonia treatment) coverage among under-five children (**Table 3**). The secondary outcome of interests are: treatment failure rate among young infants 7–59 days old with fast breathing and children 2–59 months old with chest indrawing and/or fast breathing pneumonia who received treatment from CCs; availability of essential commodities and supplies for managing childhood pneumonia; CHCPs’ knowledge of managing childhood pneumonia; caregiver’s knowledge and care-seeking practices regarding childhood pneumonia; and prevalence of pneumonia among under-five children, utilisation of CCs for pneumonia related symptoms; and treatment compliance.

**Table 3 T3:** Study enrolment and outcome assessment strategy

Activity	What	Who	When	Where	How
Case identification	Identify young infants with fast breathing pneumonia and children aged 2–59 months with fast breathing and/or chest indrawing pneumonia from data extracted from the service registers	Trained data extractors appointed by the study team	Twice in a week	Health facilities (CCs and union-level health facilities)	Trained data collectors will extract data from the registers or case record forms in the health facilities. From there, they will identify young infants with fast breathing pneumonia and children aged 2–59 months with fast breathing and/or chest indrawing pneumonia. They will provide this information to study-appointed nurses/paramedics who will conduct enrolment of the participants.
Screening and Enrolment	Enrol eligible young infants and children aged 2–59 months based on inclusion and exclusion criteria	Study appointed nurses or paramedics	One to three days after facility visit	Phone	Nurses and paramedics will screen the children based on the inclusion and exclusion criteria from the information received from study-appointed data extractors. They will contact the caregivers of the eligible children over the phone and take verbal consent for the home visit. They will enrol the children if consent is given by the caregivers.

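### Treatment compliance is scored from caregiver recall, and the container check made at the same home visits is excluded from the measure

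*Protocol article*

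**What the plan says.** All references are to the protocol article.

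- **Data analysis** fixes the measure: "We will calculate treatment compliance based on caregiver recall of giving prescribed antibiotics from CCs at home, collected through the follow-up interviews with caregivers".
- **Foreseeable strengths and limitations** names the weakness: "Another limitation will be caregiver recall of antibiotic administration, which is subject to recall and social desirability bias".
- The same section describes a physical check at the same visits: "Caregivers will be asked to show the prescription and medicine bottles during follow-up visits on days 7 and 14". Its stated purpose is "to confirm whether antibiotics were indeed prescribed to the children".
- It then excludes that check from the compliance measure: "this procedure will not be employed for assessing treatment compliance".
- The reply to the bias, given directly after, is that "we anticipate that it will minimise the recall bias, as the recall period is short". Further on, the section lists general safeguards: comparing caregiver reports with the registers, standard tools, training and audits.
- **Study outcome** lists compliance among the secondary outcomes. The objectives in Methods restrict it to children treated by CHCPs. The primary outcome is separate: "The primary outcome of interest is high (≥80%) and effective (patients receiving the full course of pneumonia treatment) coverage among under-five children".

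**The concern.** The protocol names two sources of error in recalled compliance and answers only one of them directly. A short interval helps memory. It does nothing about a caregiver who tells a visiting study nurse that the medicine was given as advised because that is the expected answer. This error is likely to run mainly one way, towards higher compliance, and a larger sample does not reduce it.

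Among the listed data sources, the container is the only physical trace of what happened at home. The nurse already asks to see it, yet the protocol rules it out for this purpose without saying why. At stake is the credibility of a stated secondary outcome, in a study meant to inform scale-up of home treatment started at community clinics.

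**Working it through.** **1. What each source can show about doses given at home**

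| Source | Where recorded | Bears on home dosing? |
|---|---|---|
| Caregiver interview, days 7 and 14 (Table 3) | Home | Yes, by report only |
| Registers or case record forms (Table 3) | Health facility | No; they show treatment provided |
| Prescription shown to the nurse | Home | No; it shows prescribing |
| Medicine bottle shown to the nurse | Home | Partly; it shows what is left |
| Independent validation of 2% of records (Quality control and assurance) | Records | The section does not describe a check of home dosing |

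Comparing the interview with the register tests whether an antibiotic was prescribed. It cannot test whether the doses were given. The bottle is the one row that adds information on the second question, and it is the one excluded.

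**2. The plan's own figures for these visits**

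The Community follow-up section sizes the visits for treatment failure, not for compliance. With n = z²p(1−p)/d² and z = 1.96:

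- 7–59 days, p = 8%, d = 4%: 1.96² × 0.08 × 0.92 / 0.04² = 176.7 (stated 176). With 5% loss, 176/0.95 = 185.3 (stated 185).
- 2–59 months, p = 6%, d = 3%: 1.96² × 0.06 × 0.94 / 0.03² = 240.7 (stated 238, about 1% lower and of no consequence here). With 5% loss, 238/0.95 = 250.5 (stated 250).

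No precision, target or expected value is stated for compliance.

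**3. Illustration of over-reporting**

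Let t be true compliance and f the share of non-compliant caregivers recorded as compliant, with no error in the other direction. Recorded compliance is then t + (1 − t)f. Both t and f are assumptions; the document gives neither.

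| True t | f = 10% | f = 20% | f = 30% | f = 50% |
|---|---|---|---|---|
| 60% | 64% | 68% | 72% | 80% |
| 70% | 73% | 76% | 79% | 85% |
| 75% | 77.5% | 80% | 82.5% | 87.5% |

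The upward shift, (1 − t)f, runs from 2.5 points (t = 75%, f = 10%) to 20 points (t = 60%, f = 50%).

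For scale, the 95% sampling half-width for a recorded proportion near 80% is 1.96 × √(0.8 × 0.2/176) = 5.9 points for the younger group, and 1.96 × √(0.8 × 0.2/238) = 5.1 points for the older group, per district under simple random sampling. At t = 70%, an f of 20% already shifts the figure by 6 points. Bias of this kind can therefore match sampling error, but whether it does so here is unknown.

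**The case against.** **The choice is disclosed and consistent.** Data analysis and the limitations section agree that recall measures compliance and that the bottle check confirms prescribing. Compliance is only described, with no test or decision rule attached. This is fair, and there is no contradiction to repair. But disclosure is a full answer only when a limitation cannot be avoided, and here a partial check is made at the same visit and set aside without a reason.

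**Other safeguards are listed.** This is true. It would be wrong to say that the short recall period is the only mitigation: the protocol also names independent data collection, triangulation, standard tools, training and audits. None of these is described as observing doses at home, so they leave the specific gap open.

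**A container check is imperfect.** This also stands. Containers may be thrown away, and an empty one does not prove that the child took the medicine. The article does not say that the registers record the quantity supplied, and it gives neither the formulation nor the course length. These limits argue against making a residual count the sole classifier. They do not argue against recording it beside recall.

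**A stronger reading to resist.** A reader might infer that over-reporting inflates the primary outcome and turns a miss into a pass at 80%. The document does not support this, for three reasons.

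- The 80% target belongs to population-based coverage, not to compliance among treated children.
- Nothing says that follow-up recall supplies the full-course element of effective coverage. Table 2 takes its coverage indicator from routine registers, and Data analysis does not define compliance as a full-course classification.
- If effective coverage is the share treated times the share completing, the arithmetic does not lead there either. With an assumed 80% treated, moving recorded completion from 75% to 90% moves coverage from 0.80 × 0.75 = 60% to 0.80 × 0.90 = 72%, below 80% both times. Even at 90% recorded completion, 0.80/0.90 = 89% of cases would have to be treated. The Household survey section assumes 40% care-seeking at baseline.

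**Conclusion.** The point holds for the secondary outcome. Compliance is calculated from caregiver recall, the protocol itself accepts that this is open to social desirability, and an available check at the same visits is excluded without explanation. Neither the short recall period nor the register comparison deals with over-reporting of doses given at home.

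The size cannot be derived from the document. The 2.5 to 20 point range above follows only from the assumed values of t and f, and it assumes that errors run in one direction. An effect on the primary outcome is possible, since no other measure of completing a course is described, but that link is an inference. This is a worthwhile and inexpensive improvement to one descriptive outcome. It is not a flaw that invalidates the study.

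**What to change.** In Foreseeable strengths and limitations, remove the statement that the container check is not used for compliance. There and in Data analysis, replace it with the following rule:

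- When a container is shown, the nurse records the medicine remaining and compares it with the amount supplied, where the register or prescription gives that amount.
- Compliance is reported both by caregiver recall and by container check, together with the agreement between the two and the share of children whose container was not available.
- Where no container is seen, recall is used.

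If the investigators judge the check unsuitable, for example because the quantity supplied is not recorded, the text should say so and give the reason.

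The cost is a few extra fields at visits already planned, plus one agreement table. Some containers will be missing, an empty container will still not prove ingestion, and the compliance figure may come out lower. No dose or treatment rule changes.
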